##### Compliance

To ensure the adherence of children in the educational intervention group during the follow-up, the game server records the information on the entry and exit of the game daily. The recorded information will be checked daily and if there is a one-week interruption in the intervention, they will be excluded from the study.

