#### Eligibility criteria

Preschool children aged 5 to 6 years old residing in Shiraz, who attend kindergartens located in Shiraz, will be recruited. Healthy children with no chronic mental, or physical illness who have educated parents will be known as eligible participants. Parents are asked about the lack of illness. In addition, eligible participants should have access to a mobile phone with the Android operating system. Disorders that make children ineligible to participate in the project include congenital disease, kidney and liver diseases, severe anemia, cardiovascular, lung diseases, either type 1 or type 2 diabetes, neurological, mental, and behavioural disorders such as autism and hyperactivity and attention deficit (ADHD), inflammatory gastrointestinal diseases, cancer, and movement disorders. Also, children with disorders requiring exceptional nutrition management will not enter the project. In the case of non-cooperating parents or children, the occurrence of any disease mentioned above and the loss of contentment or withdrawal of parents or children to continue cooperation with the project will lead to excluding the participant.

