#### Sampling method, randomization, and blinding

Using a stratified sampling method, samples will be collected from randomly selected kindergartens in different urban areas in Shiraz, Fars, Iran. Before the baseline assessment is completed, the eligible participants are randomly allocated to either the intervention (KidFood) or control group (receive no nutritional education) at a 1:1 ratio employing computer-generated random numbers. The initial and final assessor will be blind according to the assigned group of participants. Also, the statistician analyzing the data will be blind from the allocated group, with codes assigned to groups in the data set. As the trial is an educational intervention, and the control group will not receive any training, blind participants will not be feasible. Throughout the trial, the investigation team will monitor participants to prevent information transition between groups to avoid contamination bias.

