#### Sample size and power considerations

In order to provide minimum study power of 80% at the two-sided significance level (0.05), the Kid Food trial will include 120 participants (60 in each group). This sample size is determined based on KidFood-kid nutritional knowledge questionnaires.

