#### Intervention

After the development of the KidFood, Kid food-parent, and Kid food -kid nutritional knowledge questionnaire, using stratified sampling, the study will be initiated. Healthy preschool children aged 5 – 6 years old of parents or guardians who have signed the informed consent form (detail of the form will be approved by the ethics committee of SUMS) will be examined for eligibility. Then, based on the previously prepared random sequence, it will be allocated to one of the study's groups. The allocated group will be concealed in a sealed envelope and will not be revealed until the baseline assessments by the investigator. A blinded assessor will record the children's frequency of food consumption, physical activity, and anthropometric indices.

After the first assessment, the participant group will be revealed, and individuals in the intervention group will receive a text message for downloading and installing the KidFood. Following the registration of the KidFood by participants, an investigator will contact the parents of the children and guide them about how to use the game and cooperate with the project. The intervention participants will play the game for one hour per day for six months (the app will not allow playing more to prevent child inactivity).

At the end of the sixth month, participants will be asked to attend kindergarten for the final assessments, which the same investigator will do. The assessor investigator will be different from the one who is aware of the participants' group.

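### Game-arm children are excluded from the study after a one-week gap in play, a rule controls cannot trigger, so the groups compared are no longer those randomised

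*Protocol article*

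**What the plan says.** The Compliance section concerns the game arm alone: "To ensure the adherence of children in the educational intervention group during the follow-up, the game server records the information" on entry to and exit from the game. The log is checked daily, and "if there is a one-week interruption in the intervention, they will be excluded from the study". The prescribed exposure is long: "The intervention participants will play the game for one hour per day for six months".

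The section on sampling, randomization and blinding describes the other arm as a "control group (receive no nutritional education) at a 1:1 ratio employing computer-generated random numbers".

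The Eligibility criteria contain a second exclusion that operates after enrolment. It begins "In the case of non-cooperating parents or children, the occurrence of any disease mentioned above", goes on to withdrawal, and names no arm.

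The Statistical analysis section compares changes between groups with an independent-samples t-test. The article does not say that excluded children attend the six-month assessment or are analysed in their allocated group. The sample size is 60 per group, for "minimum study power of 80% at the two-sided significance level" of 0.05, based on the children's knowledge questionnaire.

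**The concern.** Randomisation makes the two groups comparable at the start. A rule that then removes children from one group because of what they did after allocation gives up that comparability. A game-arm child who stops playing for a week leaves; a control child from a similar family has no game to stop playing and stays.

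If children who keep playing would have gained more knowledge anyway, the retained game arm is favourably selected and an ineffective game can appear to work. This bears on the primary hypothesis, which is improved knowledge compared with the control group.

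The point does not turn on the article being condensed or on a statistical analysis plan that is not shown. The rule is stated, and it takes the child out of the study, not only out of the game. If it is followed literally, the six-month outcomes of these children may never be collected, and a later analysis plan cannot recover them.

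**Working it through.** **The plan's own figure.** The 60 per group cannot be reproduced, because no effect size, SD or dropout rate is given. It can be solved backwards. With two-sided alpha 0.05 and 80% power, the detectable difference is (1.960 + 0.842) × √(2/60) = 0.511 SD by the normal approximation, or 0.516 SD with the t distribution. This serves only as a scale for the bias.

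**Inputs from the article:** 60 per group, 1:1 allocation, two-sided 0.05, t-test on changes, exclusion in the game arm only.

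**Inputs assumed, because the article gives none:** the fraction f of the game arm excluded, and the correlation r between a child's adherence and the knowledge gain that child would have had anyway. For plausible f, take six months as 26 weeks and suppose an independent chance p per week of a full-week gap. Then f = 1 − (1 − p)^26, which is 12% for p = 0.5%, 23% for p = 1% and 41% for p = 2%.

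**Bias under no true effect.** If the least adherent fraction f is removed and both quantities are normal, the mean gain of those retained is shifted by r × φ(z_f)/(1 − f) SD:

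- f = 0.1: φ(−1.282) = 0.1755; 0.1755/0.9 = 0.195; r = 0.3 gives 0.06 SD.
- f = 0.2: φ(−0.842) = 0.2800; 0.2800/0.8 = 0.350; r = 0.3 gives 0.10 SD.
- f = 0.3: φ(−0.524) = 0.3477; 0.3477/0.7 = 0.497; r = 0.3 gives 0.15 SD and r = 0.5 gives 0.25 SD.
- Any f with r = 0 gives no bias. With f = 0.2, r = −0.3 gives −0.10 SD, against the game.

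**Type I error.** In simulated trials with 60 randomised per arm, no true effect, the least adherent fraction removed from the game arm only, and a pooled t-test:

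| f | r | Bias (SD) | Two-sided type I error |
|---|---|---|---|
| 0.1 | 0.3 | 0.06 | about 6% |
| 0.2 | 0.3 | 0.10 | about 8.5% |
| 0.3 | 0.3 | 0.15 | about 11% to 12% |
| 0.3 | 0.5 | 0.25 | about 24% |
| 0.3 | 0 | 0 | 5% |

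In the rows with bias most false positives favour the game, and nearly all do once f is 0.3. A bias of 0.15 SD is 0.15/0.516 = 29% of the detectable difference; 0.25 SD is 48% of it.

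**What analysis as randomised costs.** With all 120 children kept, this selection bias is zero and the type I error is 5%. If a fraction f of the game arm gains nothing (assumed), the effect estimated is 0.516 × (1 − f): 0.464, 0.413 and 0.361 SD for f = 0.1, 0.2 and 0.3. Power at 60 per arm is then 71%, 61% and 50%.

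**The case against.** **Direction and size are assumed.** This stands. A reader might infer that the result is certain to favour the game. The article does not show it: the sign follows r, which is not given. The rule also does not pick out the least engaged cleanly. A child who plays daily except for one week away is excluded, while one who opens the game briefly every few days stays. Removing exactly the lowest fraction is therefore the most selective case for a given r. Gaps caused by illness, travel or a broken phone may have little to do with motivation. If gaps cluster in some children, fewer are excluded: a mean weekly risk of 1% gives about 16% instead of 23% under one assumed beta-distributed risk.

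**Controls can be removed too.** This stands in part. The non-cooperation clause in the Eligibility criteria names no arm, so it is too much to say that every unmotivated control stays. It is not, however, an equivalent adherence test: no control is monitored daily against a one-week threshold.

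**Blinding.** A reader might infer that one-sided exclusions reveal the arms to the statistician, who works "with codes assigned to groups in the data set". The article does not say whether excluded children or the reasons for exclusion reach that data set. Unequal counts could hint at the arm, but loss of blinding is not established.

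**Power.** A reader might add that exclusions erode the stated power. With 48 v 60 or 42 v 60 analysed, power at 0.516 SD is 75% or 72%. This is no argument for the fix, because analysis as randomised may have less (61% or 50% if 20% or 30% gain nothing). The 60 per group may also already allow for attrition. The case rests on validity.

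**Conclusion.** The concern holds. A stated rule removes children from one randomised arm only, for behaviour after allocation, and nothing in the article retains them in follow-up or analysis. The loss of the randomised comparison does not depend on any assumption.

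The bias probably favours the game, but neither its sign nor its size is established. On the assumptions above it runs from none (zero correlation), through about 0.06 to 0.15 SD with type I error of about 6% to 11% (10% to 30% excluded, correlation 0.3), to about 0.25 SD and 24% (30% excluded, correlation 0.5). It needs correcting before the trial is analysed, and preferably before any six-month assessment is missed.

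**What to change.** 1. Replace the exclusion sentence under Compliance: children with an interruption in play remain in the study, have the six-month assessment, and are analysed in the group to which they were randomised. Make this the primary analysis.
2. In the Eligibility criteria, state that exclusions arising after randomisation do not remove a child from follow-up or analysis unless consent is withdrawn.
3. Use the one-week rule only to define a supportive per-protocol set.
4. Report by arm how many children met each exclusion criterion, with the reason.
5. Restate the power, giving the effect size and SD assumed, the share of the game arm expected not to play, and the number expected to have six-month data.

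The cost is a wording amendment and six-month assessments for children who would otherwise have been dropped. The estimate will probably be less favourable, because non-players dilute it, and the loss of power is not trivial: about 61% at the back-solved 0.516 SD if 20% of the game arm gains nothing. That diluted effect is the effect of offering the game, and dilution is no reason to keep the exclusion.

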### Hypotheses

The primary hypothesis is that KidFood will improve children's and parents' nutritional knowledge after six months of engagement compared to the control group. The secondary hypothesis is that KidFood players will adhere to more appropriate dietary habits, consume enough fruits, vegetables, and dairy products, and gain higher dietary diversity scores. The tertiary hypothesis believes that KidFood engagement can improve anthropometric indices in children 5 – 6 years old.

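### The one-week-interruption rule excludes randomised children from the game arm only, so children selected on behaviour after allocation are compared with controls not subject to the rule

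*Protocol article*

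**What the plan says.** The Compliance section (under Assessments) sets up the log: "To ensure the adherence of children in the educational intervention group during the follow-up, the game server records the information" on daily entry to and exit from the game. It then fixes the consequence: "if there is a one-week interruption in the intervention, they will be excluded from the study".

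Under Sampling method, randomization, and blinding, children are allocated individually "at a 1:1 ratio employing computer-generated random numbers", and the comparison arm is a "control group (receive no nutritional education"). The Intervention section asks game-arm children to play for an hour a day over six months and places the final assessment at the end of month six. The Statistical analysis section compares between-group changes with an independent-samples t-test.

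The primary hypothesis concerns "nutritional knowledge after six months of engagement compared to the control group". The Eligibility criteria section has separate exclusions after entry, beginning "In the case of non-cooperating parents or children, the occurrence of any disease mentioned above" and including withdrawal. Those are not limited to one arm.

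**The concern.** The rule acts after randomisation, depends on what the child does after allocation, and can be triggered in one arm only. A game-arm child who stops for a week through illness, a holiday or loss of interest leaves the study. The same kind of child in the control arm stays, because there is no play to interrupt. The article gives no route by which a child excluded early reaches a six-month measurement.

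Randomisation makes the two groups comparable as allocated, not after one of them has been filtered on persistence. Children who keep up daily play may differ from those who stop, for instance in how engaged their families are, and that difference could itself move the outcome. The t-test would then credit the game with a gap it did not cause. Outcomes that were never collected cannot be recovered later by any analysis plan.

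**Working it through.** **The plan's own figure.** The sample-size section gives 60 per arm, 80% power and two-sided 0.05, but no effect size, SD or dropout. So 120 can be neither reproduced nor refuted. Solved backwards, it implies a detectable difference of (1.960 + 0.842) × √(2/60) = 0.511 SD. This serves only as a yardstick.

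**Step 1: how many children might be excluded (assumption).** Take 182 days, with play on each day independent of the others. A recursion over the current run of missed days (0 to 6, leaving at 7) gives the chance of at least one seven-day gap:

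| Days played | Share excluded |
|---|---|
| 80% | 0.2% |
| 70% | 2.7% |
| 60% | 16% |
| 50% | 51% |

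In this model an exclusion share of 20-30% corresponds to play on about 55-58% of days. Illness and holidays cluster missed days, which would raise the share at a given level of play.

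**Step 2: bias when the game has no effect (assumption).** Let q be the excluded share of the game arm, taken as the least persistent, and r the correlation between persistence and outcome change. Then

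bias (SD) = r × φ(z_q) / (1 − q),

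where z_q is the q-quantile of the standard normal and φ its density. For q = 0.20 and r = 0.3: φ(−0.842) = 0.280; 0.280/0.80 = 0.350; 0.3 × 0.350 = 0.105 SD.

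**Step 3: two-sided error of the t-test.** With n₁ = 60(1 − q) children left against 60 controls, the noncentrality is bias / √(1/n₁ + 1/60). For the same case: 0.105 / √(1/48 + 1/60) = 0.105/0.194 = 0.54, and the noncentral t on 106 degrees of freedom rejects in 8.4% of trials.

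| Excluded q | Left in game arm | r | Bias (SD) | Two-sided error |
|---|---|---|---|---|
| any | – | 0 | 0 | 5.0% |
| 3% | 58 | 0.3 | 0.019 | 5.1% |
| 16% | 50 | 0.3 | 0.087 | 7.4% |
| 20% | 48 | 0.1 | 0.035 | 5.4% |
| 30% | 42 | 0.1 | 0.050 | 5.7% |
| 20% | 48 | 0.3 | 0.105 | 8.4% |
| 30% | 42 | 0.3 | 0.149 | 11.4% |
| 20% | 48 | 0.5 | 0.175 | 14.6% |
| 30% | 42 | 0.5 | 0.248 | 23.1% |

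Simulation with 20,000 trials per cell agrees (8.4% and 11.6% for q = 20% and 30% at r = 0.3). Against the 0.511 SD yardstick, a bias of 0.105-0.149 SD is 21-29% (0.105/0.511 and 0.149/0.511).

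**Step 4: all children kept.** With all 60 per arm analysed as randomised, the simulated error is 4.7-5.4% at every correlation tried, and the bias is zero.

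**Power, apart from bias.** At 0.511 SD, losing 20% of one arm gives Φ(0.511/√(1/48 + 1/60) − 1.96) = 75%, and losing 30% gives 72%. The sample-size section shows no allowance for this.

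**The case against.** The best defence is that a condensed article may leave analysis sets to a fuller document, and that the hypotheses speak of engagement and of players, so a question about adherent children may be intended. The first part would be fair if the complaint were only that no analysis set is named. But the article states a rule, and the rule puts children out of the study. The second part makes the target of estimation open to choice, but it does not make persistent players comparable with unfiltered controls.

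A second defence is that the effect may be negligible. That stands as a limit: with daily play close to what is asked, or a weak correlation, the bias is close to nil, and the documents supply neither input.

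Some stronger readings are tempting but not supported:

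- *That persistent players are compared with all controls.* The Eligibility criteria can also remove controls, for non-cooperation, new disease or withdrawal. The asymmetry lies in this one rule.
- *That every outcome is biased in favour of the game.* That follows only from assuming a positive correlation. It is plausible for knowledge. For diet and growth nothing in the article shows the sign, and the Intervention section itself caps play time out of concern about inactivity.
- *That the rule unblinds the analyst.* The plan says "the statistician analyzing the data will be blind from the allocated group, with codes assigned to groups in the data set". Unequal group counts might hint at the code, but either arm can lose children for other reasons, and nothing says that logs or excluded children appear in the analyst's data set.
- *That the six-month assessments are already arranged for these children.* The article says they are excluded and gives no such assessment.

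**Conclusion.** The concern holds as an exclusion after randomisation that can act in the game arm only. This follows from the text and needs no assumption. The size of the resulting bias does need assumptions: that the least persistent children are the ones removed, and the chosen values of exclusion share and correlation. Over the ranges tried, with no true effect, it runs from practically nothing (0.02 SD, 5.1% error) to 0.25 SD and 23% error. It vanishes if persistence is unrelated to outcome change, which the plan gives no ground to assume. Because the rule would stop outcome collection for the affected children, it should be changed in the protocol and not left to the analysis.

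**What to change.** In the Compliance section, replace the exclusion clause with wording to this effect: an interruption of one week is recorded as non-adherence; the child stays in the trial, is invited to the six-month assessment in the same way as controls, and is analysed in the arm to which he or she was randomised. Make that comparison the primary one. Results for adherent children only may be reported as a secondary analysis labelled as such, and the server log can describe play time.

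The text change is one sentence. The real costs are the effort of reaching and assessing children who stopped playing, and an estimated effect that may be smaller because those children are included.

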### Statistical analysis

All statistical analyses will be performed with the Statistical Package for the Social Sciences (SPSS) (IBM SPSS Statistics for Windows, version 23.0; IBM Corp.), with a significance set at *P* < 0.05. The normality of data will be assessed using the Kolmogorov Smirnov's test. The descriptive analysis method includes reporting mean, standard deviation, median, frequency, and percentage, which will be used to describe the data depending on the type of variable (quantitative and qualitative). A paired *t*-test will be used to compare the variables before and after each group's intervention, and an Independent-sample-*t*-test will be used to compare the between-group changes.

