## Abstract

Preschool age is a great time to learn a healthy lifestyle, for behavior therapy. Mobile health procedures are inexpensive, reliable, and accessible. This project has two phases. The KidFood mobile game and two nutrition knowledge questionnaires were designed during the first phase. In the second phase, a six-month, parallel, blinded, randomized controlled trial will perform on 120 Iranian children aged 5 to 6 years. Before and after nutritional education via KidFood, the dietary habits, the nutritional knowledge of parents and children, and the anthropometric indices of children will be evaluated.

Specifications table

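### The group effect is tested by an unadjusted t-test on change scores although baseline is collected; ANCOVA on baseline would be more precise, mainly for the knowledge and dietary outcomes, at no cost

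*Protocol article*

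**What the plan says.** The Statistical analysis section of the protocol article names two inferential tests. A paired t-test "will be used to compare the variables before and after each group's intervention", and an independent-samples t-test "will be used to compare the between-group changes". No covariate or regression model is mentioned.

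Baseline values exist. The Abstract states: "Before and after nutritional education via KidFood, the dietary habits, the nutritional knowledge of parents and children" and the children's anthropometric indices are to be evaluated. The Intervention section places the first assessment before the allocated group is revealed, so baseline is a proper pre-treatment covariate.

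The primary hypothesis is a comparison between arms: the game is to "improve children's and parents' nutritional knowledge after six months of engagement compared to the control group".

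On sample size, the article plans 60 children per arm for at least 80% power at two-sided 0.05 and adds: "This sample size is determined based on KidFood-kid nutritional knowledge questionnaires". It gives no difference, SD or correlation, and does not say whether the power refers to the six-month score or to the change.

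**The concern.** A t-test on changes subtracts the whole baseline value, which amounts to a regression with the baseline slope set at 1. That is the best slope only for a particular combination of correlation and spread. Several outcomes here are noisy or bounded: a 40-item picture test in children of 5 to 6 years, a three-day food record, and a diversity score from 0 to 10. For such measures a six-month correlation close to 1 is not to be expected. Subtracting all of baseline then adds noise to the comparison, and an arm that happens to start low appears to gain more.

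The paired tests raise a separate question. Children grow and learn over six months in both arms, so a change within one arm does not estimate the effect of the game. A contrast between two within-arm P values is not a test of that effect either.

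At stake are the width of the confidence intervals and the dependence of the estimate on chance baseline differences.

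**Working it through.** **Inputs from the protocol article.** 60 per arm, 1:1 allocation, two-sided 0.05, power at least 80%, and the two t-tests above.

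**Assumptions.** The correlation r between baseline and six months is not given; 0.3, 0.5 and 0.7 are shown as a range. SDs are taken as equal at both times (σ).

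**The plan's own figure.** The total of 120 cannot be reproduced, because no effect size or SD is stated. Solving backwards, 60 per arm gives 80% power for a standardised difference of (1.960 + 0.842) × √(2/60) = 0.511 by the normal approximation, or 0.516 for the t-test. The steps below use 0.511.

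**Variance of the group effect, in units of 2σ²/n**
- Six-month score alone: 1
- Change score: 2(1 − r)
- ANCOVA: 1 − r², times 1 + 1/(120 − 4) = 1.0086 for estimating the slope
- Ratio of ANCOVA to change score: (1 − r²) / [2(1 − r)] = (1 + r)/2

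| r | Change | ANCOVA (large sample) | Ratio | Ratio with slope cost | Ratio in 20,000 simulated trials | CI narrower by 1 − √ratio |
|---|---|---|---|---|---|---|
| 0.3 | 1.40 | 0.91 | 0.65 | 0.656 | 0.652 | 19% |
| 0.5 | 1.00 | 0.75 | 0.75 | 0.756 | 0.759 | 13% |
| 0.7 | 0.60 | 0.51 | 0.85 | 0.857 | 0.853 | 8% |

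Under equal SDs, the change score is less precise than ignoring baseline when 2(1 − r) > 1, that is, when r < 0.5.

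**Limits of the ratio.** At r = 0.95 it is 0.975 (0.983 with the slope cost), about 1% of CI width. With 120 children the break-even is r = 2/1.0086 − 1 = 0.983. Above it the change score is ahead by less than 1% of variance (ratio 1.004 at r = 0.99).

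**Power under the two readings of the 80%.** Power = Φ(δ / √(V × 2/60) − 1.960), where V is the variance factor with the slope cost included for ANCOVA, and δ is in units of σ.

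*Reading A, 80% on the change score:* δ = 0.511 × √[2(1 − r)]. *Reading B, 80% on the six-month score:* δ = 0.511.

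| r | A: planned test | A: ANCOVA | B: planned test | B: ANCOVA |
|---|---|---|---|---|
| 0.3 | 80% | 93.3% | 65.8% | 83.3% |
| 0.5 | 80% | 89.6% | 80.0% | 89.6% |
| 0.7 | 80% | 85.7% | 95.1% | 97.4% |

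Under reading A, and leaving out the small slope cost, ANCOVA reaches 80% with 39, 45 or 51 per arm instead of 60.

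**Chance imbalance.** The baseline difference between arms has a standard error of √(2/60) = 0.183 SD. A difference of 0.2 SD or more in either direction has probability 2[1 − Φ(0.2/0.183)], about 27%. Given a baseline difference Δ, the change-score estimate shifts by −(1 − r)Δ; the simulated slopes were −0.70, −0.50 and −0.30 at r = 0.3, 0.5 and 0.7. At r = 0.5 and Δ = 0.2 SD the shift is 0.5 × 0.2 = 0.1 SD, about one fifth of 0.511. The ANCOVA estimate showed no correlation with Δ at any r tried.

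**The case against.** The strongest defence is that the planned between-group test is sound. Over randomisation it is unbiased, it controls type I error, and it addresses the stated hypothesis. That stands, and it makes this a point about efficiency and not about validity.

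Four stronger readings are tempting, and the article does not support them.

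- **ANCOVA gains at every correlation and on every outcome.** The article reports no correlations. Weight, height and BMI may be so stable over six months that almost nothing is gained, and at this sample size the advantage reverses very slightly above r of about 0.98. The (1 + r)/2 ratio also needs equal SDs. In general the change-score variance exceeds the ANCOVA variance by an amount proportional to (s1 − r·s2)², with s1 and s2 the SDs at baseline and six months. This is zero when s2 = s1/r, so the change score could be fully efficient if spread increases enough with age. In large samples it is never better than ANCOVA.
- **The trial is underpowered.** A shortfall arises only if the sample size was set on the six-month score and r is below 0.5. If it was set on the change score, which is the analysis actually planned, the stated power holds and ANCOVA only adds to it.
- **Adjustment removes baseline imbalance, or corrects regression to the mean.** It removes the conditional bias that imbalance in the adjusted variable causes, not the imbalance itself. Regression to the mean is equal in expectation in randomised arms and matters only through chance imbalance.
- **The paired tests will be used to claim efficacy.** The Statistical analysis section gives the between-group question to the independent t-test, and nothing says that within-arm significance will support a claim.

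It may also be said that a condensed article can leave adjustment to an analysis plan. Here, though, the article names the test, so this is a stated choice and not an omission.

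**Conclusion.** The point holds as an improvement to a stated method. The planned test is valid but gives up precision and leaves the estimate exposed to chance baseline differences, while the data that would prevent both are already collected. For the knowledge and dietary outcomes the gain is material if r lies between 0.3 and 0.7: confidence intervals 19% to 8% narrower before the small slope cost. For highly stable anthropometry it is small. ANCOVA has the higher power under both readings of the 80% at these correlations. The sizes rest on an assumed r and on equal SDs, neither of which can be checked from the article. The within-arm paired tests do not address the primary hypothesis and are useful only as description.

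**What to change.** In the Statistical analysis section, replace the independent t-test on changes with a linear model (ANCOVA) of the six-month value on group and the baseline value of the same variable. Report the adjusted group difference with its 95% CI. Add age and sex as covariates for raw weight and height only, because the Growth indices section already adjusts BMI for both through BMI-for-age percentiles. State that before/after results within each arm are descriptive and are not tests of the effect of the game.

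The cost is a sentence or two of text. No further data or children are needed, and SPSS, which the article already names, fits the model.
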